## Abstract

**Background:**

Routine use of brief, structured screening tools is essential to detect and provide support for Australians who drink above recommended levels. However, detecting drinking above recommended levels in Aboriginal and Torres Strait Islander Australian primary care settings is complex. Inaccuracies in completing a screening tool such as Alcohol Use Disorders Identification Test - Consumption, can lead to errors in estimating drinking in First Nations contexts where group sharing and episodic drinking make it difficult to accurately estimate alcohol consumption with tools that assume regular drinking patterns. This can lead to under-detection of drinking and a mismatch with the subsequent care that is offered. Hence, screening tools that consider these contextual factors are needed to make it easier for First Nations Australian primary care services to screen for alcohol consumption above recommended levels. Electronic screening tools offer the technical flexibility to consider the drinking contexts Furthermore, for sensitive topics such as alcohol and other drugs, computer-based screening in the general population has been shown to provide more accurate and comprehensive responses compared with face-to-face interviews.

**Aim:**

To facilitate alcohol screening and brief intervention in First Nations Australian primary care settings by adapting the Grog App – a community survey tool validated in Aboriginal and Torres Strait Islander populations for use in primary care.

**Methods:**

The project will use mixed-methods techniques across five study stages: 1 – Interest-holder consultation; 2 – technical development; 3 – re-validation and user interface acceptability; 4 – implementation in an Aboriginal and Torres Strait Islander primary care setting; 5 – acceptability study, six months after implementation.

**Discussion:**

The project will produce a novel, culturally appropriate digital health tool and implementation resources to make it easier to conduct routine alcohol screening in primary care contexts for a priority population, which may lead to increased screening and alcohol care rates. It will also provide first-ever contextual data about implementation of new health service improvement strategy focused on an electronic alcohol consumption screening tool, which is lacking in peer-reviewed literature. This study will also provide an important evidence base for using continuous quality improvement as an implementation approach in primary care settings.

## Background

Screening and brief intervention can be effective in reducing alcohol consumption in general populations [1, 2]. Yet, structural inequities make detecting drinking above recommended levels complex in First Nations Australian primary care settings [3]. First Nations clients may be less comfortable answering questions one-on-one about their alcohol use due to racism, shame, or fear of adverse consequences, such as child removal; all genuine concerns arising from the enduring consequences of colonisation [4]. It can also be uncomfortable for First Nations Australian health professionals to screen their family members or close friends, which may be considered “getting in too close” [5].

Often, individuals do not ask for help about their drinking, which may go undetected [6]. Thus routine use of brief, structured screening tools is essential to detect and provide support for First Nations Australians who drink above recommended levels [7]. Australian guidelines recommend that First Nations Australians receive screening with a validated tool ‘as part of an annual health assessment, or opportunistically’, or more frequently in high-risk groups [8]. However, uptake and use of screening tools in First Nations Australian primary care is inconsistent [9]. Screening has been shown to occur selectively such as when the client presents under the influence of alcohol or with alcohol-related injuries [6, 10]. Recent randomised trial data showed that in Aboriginal Community Controlled contexts, more than 50% of AUDIT-C screens recorded were offered as part of annual adult health checks for which clients need dedicated appointments [10]. Another analysis of the same study found that while nearly half of clients who visited the services at baseline and during implementation were not screened at all, others were screened repeatedly [11].

While routine screening is demonstrated to have benefits, it is unclear which screening tool (if any) is appropriate for clinical use as few have been validated with First Nations Australians [3]. AUDIT-C (the first three items of the Alcohol Use Disorders Identification Test) [12] is most frequently used with First Nations Australians in clinical settings. However, when screening is conducted, inaccuracies in completing AUDIT-C can result in under detection of drinking and a mismatch with the subsequent care that is offered [3, 13]. AUDIT-C typically requires the clinician to record the number of Australian ‘standard’ drinks consumed (each of 10 g ethanol). However, this requires both the client and clinician to know the volume and strength of the beverage consumed, size of a standard drink, and possess the required mathematical skills to do the calculation. Errors when completing these calculations are common [14]. Furthermore, estimating drinking can be harder in First Nations contexts where alcohol is often shared in groups and often occurs episodically [15] —making it difficult to (i) accurately track individual consumption and (ii) calculate standard drinks from non-standard drinking containers [15]. This, in turn can make it harder to answer questions on ‘usual’ quantity or frequency of consumption, such as in AUDIT-C. Hence, screening tools that consider these contextual factors are needed to make it easier for First Nations Australian primary care services to screen for alcohol consumption above recommended levels, especially when there may be no ‘usual’ drinking pattern [15]. For sensitive topics such as alcohol and other drugs, computer-based screening in the general population has been shown to provide more accurate and comprehensive responses compared with face-to-face interviews [16]. This digital tool approach has already proved successful with First Nations Australians, as ‘The Grog Survey App’ (Grog App), a population screening tool for drinking.

The Grog App is a digital survey tool, developed with First Nations Australian primary care services, drug and alcohol health professionals, community members and researchers [4]. The Grog App assesses self-reported alcohol use using: (i) a modified pictorial version of AUDIT-C [17] and a modified ‘Finnish’ method [17] that asks about the last four drinking occasions in the past 12 months; (ii) frequency of dependence symptoms (3-items derived from World Health Organization’s International Classification of Diseases 11th Revision core features) [18]; and (iii) harms from drinking. An interactive format allows individuals to select images of alcohol consumed and containers used, to indicate container fullness, and (where preferred) to describe their drinking based on what the whole group drank. The digital interface offers privacy to answer potentially sensitive questions, while also overcoming literacy barriers by delivering questions in male or female, English or Pitjantjatjara voiceover (Aboriginal language commonly spoken in parts of South Australia, Northern Territory and Western Australia) [19].

While the Grog App has been shown to be an accurate, reliable [20] and acceptable [19] tool to measure alcohol consumption among First Nations Australians in community surveys, it may have wider applications that are yet to be explored including its use as a clinical tool. The Grog App could help make screening more efficient and accurate, while also delivering tailored brief interventions and health education [19]. The Grog App could also help increase screening uptake in First Nations Australian primary care services, which have remained low despite considerable effort [21]. In this paper, we outline a protocol for testing the Grog App as a tool to improve screening for alcohol consumption in primary care.

### Aim

This study aims to facilitate alcohol screening and brief intervention by adapting the Grog App for use in primary care settings. Screening results will also be made available to the primary care clinician via clinical practice software.

## Methods

### Overall design

The project will use mixed-methods techniques across five study stages (Fig. 1), to address the aim described above. Throughout the project, the stages will involve First Nations Australian and non-Indigenous interest holders to co-create an electronic screening tool, test technical solutions, develop implementation strategies, test acceptability for staff and clients and to disseminate the final Grog App. The project will include the following stages:

Stage 1 – Interest holder consultation on the redesign of the original Grog App for primary care purposes via interest holder forum and a Delphi study [22].Stage 2 – Develop the technical solution for the modified app and connection to general practice software (‘Best Practice’).Stage 3 – Re-validate the app for screening sensitivity and specificity in a private primary care clinic with a high proportion of First Nations Australian clients, and test user interface acceptability.Stage 4 – Implement the modified Grog App at a pilot First Nations Australian primary care site using continuous quality improvement (CQI), to enable us to determine an optimal implementation strategy.Stage 5 – Assess acceptability of the new app in the implementation site six-months post implementation.

**Fig. 1 Fig1:**
[figure not shown]
The relationship between study stages and their outcomes Blue boxes designate project stages; green boxes designate stage outcomes

### Ethics, governance and community participation

This project has arisen in response to the need to adapt the Grog App, highlighted by the Southern Queensland Centre of Excellence in Aboriginal and Torres Strait Islander Primary Health Care, known as Inala Indigenous Health’ Service (NH); The project has sought and received endorsement from Marrin Weejali Aboriginal Corporation representing the study site in New South Wales (NSW), and in Queensland via Inala Community Jury for Health Research (Inala Community Jury). Subsequently, ethical approval was obtained from the Aboriginal Health and Medical Research Council of New South Wales (NSW; approval no. 2076/23), and Metro South Health, Queensland Human Research Ethics Committee (Qld, approval No. REC/2023/QMS/100707, REC/2023/QMS/100707).

Project governance (Fig. 2) has been designed to prioritise First Nations Australian perspectives while maintaining close collaboration, exchange of ideas and ongoing dialogue between First Nations Australian and non-Indigenous investigators and collaborators. Project governance consists of the following committees:

A project steering committee – to oversee project delivery, comprised of a representative from each collaborating institution as well as the project management group as ex-officio members.An Aboriginal advisory group – to oversee project delivery to ensure cultural safety.Scientific advisory group – comprising all chief and associate investigators and provides academic oversight of the project.A project management team – responsible for day-to-day project management.

The committees are supported by expert working groups who will be engaged when their expertise is needed to inform each stage of the project. These include:

First Nations Australian community group.Clinician expert group (including KC, MT, LB).Technical development group (including [name], KL, JC, MT).Knowledge translation group (including SW, KL, NH, LB, TR).

All groups and committees comprise First Nations Australian and non-Indigenous members and are co-chaired by First Nations Australian and non-Indigenous investigators.

**Fig. 2 Fig2:**
[figure not shown]
Project governance

### Participant consent

We will provide research participants, including service staff and clients with participant information and consent forms (PICF) for every stage of the study. Participant-facing material will be written in plain English and reviewed by the communities and services where these will be implemented.

Given this research explores a sensitive topic (alcohol use), the process of recruiting health service clients and gaining their informed consent will be a multi-step process that begins at the point of engagement with potential participants. This method ensures that participants have time to consider whether they want to take part in the study even before they encounter the Grog App:

Local health service staff with whom the clients are familiar (e.g. Aboriginal health workers, reception staff, doctor, nurse) will approach clients aged 16 or over, when they arrive at the clinic to tell them about the study and provide them with the PICF.Health service staff will ask clients if they have any questions and want to participate.If willing to participate, clients will complete the consent forms in paper-and-pen format and/or via the Grog App and be introduced to the research team member.

### Data management

A data management plan will be developed in line with the FAIR principles (findable, accessible, interoperable, and reusable) [23], the Global Indigenous Data Alliance’s (GIDA) CARE principles (Collective benefit, Authority and control, Responsibility, and Ethics) [24] and the Australian Code for the Responsible Conduct of Research 2018 [25] as guidance.

Accordingly, the participating services will co-design data collection strategies and will remain in control of data collection. They will retain joint ownership of research datasets arising from the study. Services will be consulted on drafts of all analyses and interpretation prior to dissemination of findings. Contribution on all publications will be acknowledged without identifying individual services unless they request to be named. The data management plan has been developed as part of the study protocol and includes procedures for data collection design, data aggregation, secure storage and analysis, data privacy and data governance.

### Stage 1 – interest holder consultation

This stage consists of interest holder consultation and a Delphi study. The interest holder consultation will be delivered via a two-day workshop that aims to elicit broad suggestions for adapting the original Grog App for primary care settings. Interest holder representatives from around Australia will be invited to attend with well-balanced representation of Indigenous and non-Indigenous, state/territory, as well as professional, comprising general and specialist health care professionals, community leadership, and researchers. Prior to the workshop, participants will receive information including: (i) a demonstration (demo) version of the original Grog App if they have access to an iPad tablet; (ii) questions to get forum attendees to reflect on how health professionals ask about drinking in primary care context; and how the Grog App can help with alcohol screening in this setting. Participants will have further opportunities to familiarise themselves with the existing, unmodified, Grog App during the workshop. Subsequently, a series of breakout sessions and whole group discussions will collect feedback on themes focused on modifying original Grog App features and functionality. Discussions will be recorded by scribes. The notes will be coded in NVivo and analysed to identify key themes to inform the Delphi study.

We chose to conduct a Delphi study over other techniques as it allows consensus to be built systematically and asynchronously. The Delphi study will consist of three survey rounds, with the first round introducing the ideas arising from the forum, and at least two subsequent survey rounds to resolve non-consensus.

A panel of experts will vote on how much they agree on the importance of certain app question items. The expert panel will comprise 8–12 health professionals. Eligibility criteria will be as follows: (i) aged 18+; (ii) minimum of five years of relevant health professional experience in First Nations Australian primary care, or drug and alcohol; (iii) basic computer proficiency with reliable computer and internet to access an electronic survey platform; (iv) at least 50% of panellists will identify as First Nations Australian. Recruitment will be via purposive sampling using investigator and partner networks.

Results will be descriptively analysed after each survey round. Consensus will be set at 80% agreement. Qualitative data will be coded in NVivo for themes and undergo content analysis. Aggregated de-identified visual feedback will be emailed to panellists after each round. Results from each survey round will directly inform the questions of the next survey.

### Stage 2 software adaptation and development

Based on the feedback received in Stage 1, technical work will be conducted to adapt the Grog App. This includes collaborating with the practice software developer to enable the Grog App to communicate seamlessly with their system. Technical work will be performed by the Digital Innovation TechLab team at the University of Sydney [26], with guidance from the practice software team and the project’s Technical Working Group.

A key focus of this stage will be uplifting the Grog App with FHIR (Fast Healthcare Interoperability Resources) compliant API (application programming interface) capabilities. This will ensure that the app can meet modern healthcare data standards to enable better integration with electronic medical record (EMR) systems.

The Designing for Dignity framework developed at ICT TechLab (Table 1) will guide the design process. This framework prioritises access and use of the technology developed regardless of individual functional needs and has been successfully operationalised in mental health research [27]. Our focus will be to build an inclusive web application that is based on principles of accessibility, empowerment, and usability.

An iterative approach will ensure that user feedback is continuously integrated into the design process, resulting in an application that is effective and user-friendly.

**Table 1 Tab1:** Designing for dignity framework

Framework domain	Implementation principles
Prevalent use cases	Identify and analyse common user interactions and user groups to ensure that every function is intuitive and easily navigated.
Pathways to action	Create multiple ways for people with different abilities to complete the app, such as alternative input methods, guided assistance, and customisable settings.
Empowerment	Give users control over their data, with transparent access to their information, consent-based interactions, and options to manage their engagement with the application.
Inclusive design	Embed accessibility features and adaptive user flows to accommodate cognitive and physical impairments.
User-centred testing	Engage diverse user groups in iterative testing to validate that design choices align with real-world needs and lived and living experiences.

### Stage 3 – clinical revalidation of Grog app

A clinical re-validation study will be conducted at the Kildare Road Medical Centre, an urban primary care site in Western Sydney (NSW). This service provides care to up to 2000 Aboriginal and Torres Strait Islander Australian clients (aged 16+) annually. Clients who identify as Aboriginal and/or Torres Strait Islander and are 16 years of age or older will be recruited to complete the Grog App when they present at the clinic, and to talk with a First Nations Australian health professional or a general practitioner about their alcohol consumption. The comparison will be against their routine practice to screen for alcohol use. Sensitivity and specificity analyses will compare the Grog App screening responses to that of clinician screening. A minimum sample size of 188 participants is required to measure a sensitivity/specificity of 90% with acceptable accuracy [95% CI 80%, 100%; delta = 0.1]. This sample will allow us to detect statistically significant Pearson correlations as small as *r* = 0.2 which is sufficient. To provide an attrition buffer, a total sample of 200 participants will be recruited. User acceptability data will also be collected and fed back to the technical working group and developer team for any adjustments.

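### Stage 3 reports sensitivity and specificity against routine clinician screening, which the article itself says can under-detect drinking, so the app's specificity could be understated

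*Protocol article*

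**What the plan says.** In the protocol article, Stage 3 asks clients to complete the app and "to talk with a First Nations Australian health professional or a general practitioner about their alcohol consumption". It continues: "The comparison will be against their routine practice to screen for alcohol use". The analysis is then fixed: "Sensitivity and specificity analyses will compare the Grog App screening responses to that of clinician screening". The sample size of 188 (200 with an attrition buffer) is justified by a sensitivity/specificity of 90% with a 95% CI of 80% to 100%. No other reference is described.

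The Background describes how such screening performs in this population:

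- AUDIT-C "is most frequently used with First Nations Australians in clinical settings", and "inaccuracies in completing AUDIT-C can result in under detection of drinking and a mismatch with the subsequent care that is offered".
- On the standard-drink arithmetic that AUDIT-C needs: "Errors when completing these calculations are common".
- On disclosure to a clinician: "First Nations clients may be less comfortable answering questions one-on-one about their alcohol use due to racism, shame, or fear of adverse consequences".
- On the alternative mode: "computer-based screening in the general population has been shown to provide more accurate and comprehensive responses compared with face-to-face interviews".

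The Abstract repeats the point about under-detection. The Limitations section does not mention the choice of reference.

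**The concern.** Sensitivity and specificity are accuracy measures only if the reference can stand in for the truth. Here the reference is the kind of screening the app is meant to improve on. A client who drinks above recommended levels (a drinker, for short), is missed by the clinician and is found by the app enters the table as an app false positive. Better detection by the app then lowers its reported specificity. A larger sample does not help, because it only estimates the same quantity more precisely.

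The stake is what Stage 3 can conclude. It is the re-validation step before the app enters routine practice in Stage 4, and the Discussion lists clinical re-validation as a project outcome. As planned, agreement with an imperfect screen would be reported as accuracy.

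**Working it through.** **The plan's own figure.** The precision formula n = z²p(1−p)/d² with p = 0.90, d = 0.10 and z = 1.96 gives 34.6, so 35 participants in the relevant reference group. The total of 188 follows if about 18.4% are reference-positive (34.57/188 = 0.184). That proportion is not stated and may sit in the full protocol, so 188 is not disputed here. The point below does not depend on it.

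**Inputs for the bias.** The article gives no prevalence (p), clinician sensitivity (Sc) or clinician specificity (Pc), so all three are assumptions. The app's true sensitivity and specificity are set to Sa = Pa = 0.90, matching the planning value. Errors are first taken as independent given true status.

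**Formulas.**

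- Apparent specificity = [p(1−Sa)(1−Sc) + (1−p)PaPc] / [p(1−Sc) + (1−p)Pc]
- Apparent sensitivity = [pSaSc + (1−p)(1−Pa)(1−Pc)] / [pSc + (1−p)(1−Pc)]

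**Results with Pc = 0.95.**

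| p | Sc | Apparent specificity | Apparent sensitivity |
|---|---|---|---|
| 0.20 | 0.80 | (0.004 + 0.684)/(0.040 + 0.760) = 0.860 | (0.144 + 0.004)/(0.160 + 0.040) = 0.740 |
| 0.40 | 0.60 | (0.016 + 0.513)/(0.160 + 0.570) = 0.725 | (0.216 + 0.003)/(0.240 + 0.030) = 0.811 |
| 0.60 | 0.60 | (0.024 + 0.342)/(0.240 + 0.380) = 0.590 | (0.324 + 0.002)/(0.360 + 0.020) = 0.858 |

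**Which part is due to under-detection.** With Pc = 1, apparent sensitivity returns to 0.90 in every row, so the loss in that column comes entirely from the assumed 5% of clinician false positives. The loss of specificity remains: at p = 0.40 and Sc = 0.60 it is (0.016 + 0.540)/(0.160 + 0.600) = 0.732. Only the specificity column therefore illustrates the under-detection the article describes.

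**In participants.** In the middle row with 200 clients, 200 × 0.73 = 146 are clinician-negative. The app is positive in 200 × (0.4 × 0.9 × 0.4) = 28.8 of them who are drinkers, and in 200 × (0.6 × 0.1 × 0.95) = 11.4 who are not. About 29 of the 40 apparent false positives would be correct detections.

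**Correlated errors.** Take p = 0.40, Sc = 0.70 and Pc = 1.

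- Independent errors: apparent specificity is (0.012 + 0.540)/(0.120 + 0.600) = 0.767, and apparent sensitivity is 0.90.
- Every app miss is also a clinician miss: apparent specificity is (0.040 + 0.540)/(0.120 + 0.600) = 0.806, and apparent sensitivity is 1.00 against a true 0.90.

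Shared misses shrink the error in specificity and create one in the opposite direction in sensitivity.

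**The case against.** The strongest reply is that comparison with current practice is a legitimate concurrent-validity question. The article calls itself a pilot, cites earlier accuracy evidence for the app from community surveys, and makes no claim in Stage 3 that the app beats the clinician. This stands, and it is a reason to keep the comparison. It does not justify labelling the result sensitivity and specificity.

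Several stronger readings are tempting, but the article does not support them:

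- **That the app is bound to show poor specificity.** The Background says under-detection can occur and gives no rate. At low prevalence with mild under-detection the loss is about 4 points (0.90 to 0.86).
- **That the site uses AUDIT-C.** Stage 3 does not name its tool. The link is an inference from the Background, although the disclosure problem applies to any one-on-one screen.
- **That 90% is a pass mark.** It is a planning value for precision, and no decision rule is attached to it.
- **That low specificity would send the app back to developers or shift a cut-off.** Stage 3 feeds user acceptability data back to the developers, and no threshold derivation is planned.
- **That there are two rival comparators.** The conversation with a clinician may simply be the routine screen. One clarifying sentence would settle it.
- **That computer-based screening is known to be more accurate here.** The cited evidence concerns the general population.

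The doubt about independent errors also stands, because both measures rest on self-report. It changes the size and pattern of the bias, but does not make the reference suitable.

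**Conclusion.** The concern holds in a limited form. The article fixes routine clinician screening as the reference for accuracy measures, and elsewhere gives reasons to expect that such screening can miss drinkers. Specificity could therefore be understated.

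The amount cannot be fixed from the article. For an app truly at 90%/90%, the illustrations run from about 86% down to 59%. They rest on assumed prevalence of 20% to 60%, clinician sensitivity of 60% to 80%, clinician specificity of 95% and independent errors. If both measures miss the same people, the loss of specificity is smaller and the app's sensitivity is overstated. The article does not establish that the app will look poor, or that any decision would go wrong as a result. What needs correcting is the name and interpretation of the Stage 3 estimates.

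**What to change.** Keep the data collection as it is and change the analysis and reporting:

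1. Report positive and negative percent agreement with routine clinician screening, with 95% CIs, in place of sensitivity and specificity. State in one sentence what the routine screen is and whether the clinician conversation is that screen.
2. Add a paired comparison of detection: both discordant cells, McNemar's test, and the difference in proportions positive with a 95% CI. Read it as a difference in detection and not as proof of greater accuracy. In the 200-client illustration above, 11.4 of the 40.2 app-only positives are not drinkers.
3. Restate the 90% (95% CI 80% to 100%) planning value as a precision target for agreement.
4. List the imperfect reference, and the possibility of shared misses, under Limitations.

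The cost is wording and a small added analysis of data already planned. The downside is a more modest claim, of agreement rather than accuracy. Keeping the accuracy terms would need a reference distinct from the routine screen. That would change data collection and add burden on a sensitive topic, and the correction proposed here does not require it.
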